#### Setting, Participants, Recruitment, and Enrollment

Pilot testing will occur among WWH at the same Miami MWCCS clinical site where phase 2 focus groups occurred. The clinic is one of the largest hospital-based clinics in Miami, a city with one of the highest rates of incident and prevalent HIV infections in the United States. We will recruit 180 women from the existing client population over the course of 15 months (about 12 women per month). A full-time research associate will approach potential participants at their regular clinic visit, share information about the study, and invite them to take part in eligibility screening. Participants must meet the following eligibility criteria: (1) identify as female; (2) be receiving HIV-related care at the Miami site; (3) have a diagnosis of HIV infection; (4) aged 18 and older; (5) be interested in learning about LAI ART and open to discussing HIV treatment with their provider; and (6) be willing to provide informed consent.

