**Primary**			Assessed after *i.ARTs* use among women using i.ARTs (n=90)
	Feasibility	Adaptation of Thabane et al’s [59] framework [60,61] for assessing pilot studies: Process, Resources, Management, Science	
	Acceptability and usability	Acceptability [62] and CSQ-8^b^ [63] to measure satisfaction with *i.ARTs*; exit interviews about *i.ARTs* features/protocol [62]	
**Secondary**			Assessed in baseline survey and postvisit survey for all women (n=180)
	Decisional conflict	Decisional Conflict Scale (16 items) [52]; satisfaction with the chosen method [64]	
**Tertiary**			Assessed 1-year prebaseline, at baseline, 3 months, and 6 months (all women; n=180)
	Viral suppression	Viral suppression, defined as viral load below limit of detection per assay used	
	Medication refills	Missed doses; report of medication refills/pharmacy pick up (WWH^c^ on oral ART^d^)	
	Clinic attendance	Missed or cancelled medical visits (<2 visits in a 6-month period for oral ART; missed monthly visit for LAI^e^ ART)	
	ART modality	Adoption of LAI among patients who are virally suppressed	
**Moderators**			Assessed at baseline
	Sociodemographics	Race/ethnicity, age, housing stability, education, employment, income, distance from clinic, relationship status, children	
	Depression/anxiety	PHQ-8^f^ (depression) [65]; GAD-7^g^ [66]	
	Substance use	ASSIST^h^ [67], an 8-item measure of problematic substance use	
	Stigma/discrimination	MDS^i^ to measure racial discrimination [68]; HIV-related stigma	
	Self-efficacy	HIV-ASES^j^ [38]	
	ART-related knowledge	Adaptation of Feldman’s [69] scale of oral ART knowledge; BMQ^k^ [70]	

^a^*i.ARTs*: i.ART+support.

^b^CSQ-8: 8-item Client Satisfaction Questionnaire.

^c^WWH: women with HIV.

^d^ART: antiretroviral therapy.

^e^LAI: long-acting injectable.

^f^PHQ-8: 8-item Patient Health Questionnaire.

^g^GAD-7: 7-item General Anxiety Disorder scale.

^h^ASSIST: Alcohol, Smoking and Substance Involvement Screening Test.

^i^MDS: 10-item Multiple Discrimination Scale.

^j^HIV-ASES: HIV Treatment Adherence Self-Efficacy Scale.

^k^BMQ-18: 18-item Beliefs and Medicines Questionnaire.

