#### Study Outcomes and Measures

All study outcomes are summarized in Table 2. *Primary outcomes* include *i.ARTs feasibility, acceptability,* and *usability.* To assess feasibility, we will adapt Thabane et al’s [59] framework [60,61]. For *acceptability and usability,* we will use the 8-item Client Satisfaction Questionnaire (CSQ-8) to assess participants’ attitudes, burden, ethics, coherence, opportunity cost, perceived effectiveness, and self-efficacy [63]. The *secondary outcome* is ART-related decisional conflict, a 16-item scale scored from 0 to 100 [52]. Scores of 0-25 are associated with “implementing decisions” and scores of 37.5-100 are associated with “decision delay/feeling unsure.” *Tertiary outcomes* are exploratory, and consist of information extracted from EMRs, including viral suppression at the most recent visit in the prior 6 months, ART modality, medication refills (oral ART), and clinic attendance in the prior 6 months.

In addition to the outcomes, the baseline survey will measure moderators associated with adherence, including sociodemographics, depression, anxiety, substance use, HIV-related stigma and discrimination, self-efficacy, and ART-related knowledge.

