#### Analysis

The primary outcomes of feasibility, acceptability, and usability will be assessed descriptively. We will compare ART-related decisional conflict, clinic attendance, viral suppression, and medication refills between and within the 90 women in each arm (baseline vs postvisit surveys and EMR data at 3 and 6 months). For normally distributed data, we will first use *t* tests to compare the 2 arms and then use regression methods to develop a multivariable model of the outcome, with arm membership as the principal covariate, while controlling for the moderators listed in the previous sections and in Table 2. For nonnormally distributed data, we will employ chi-square tests and logistic regression; distributional properties of the outcome will determine the type of logistic regression (eg, binary, multinomial, or ordinal logistic regression models). We note that these are examples and the final approach will be determined based on the distribution of the data.

The primary analysis will use an intent-to-treat approach with the use of *i.ARTs* as a 1-time exposure, with α=.05, and 2-sided tests. The number of moderators included in the regression model will be used to make a Bonferroni adjustment to the α value. A secondary efficacy analysis will explore actual treatment taken. Our exploratory tertiary outcomes of viral suppression, clinic attendance, chosen ART modality, and medication refills will compare both between and within *i.ARTs* and control arm women (ie, baseline and postvisit surveys and EMR data at 3 and 6 months); we will also examine these outcomes for women who do not change regimens. We will use prebaseline EMR data to control for previous viral load. We will also compare how many women in each arm change modalities postbaseline to assess *i.ARTs’* accuracy in identifying which HIV treatment modality is the best match. Sensitivity analyses will determine whether assumptions associated with each model are defensible.

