#### Power Analysis and Sample Size

Our sample size is based on our secondary outcome of decisional conflict, as our primary outcomes of acceptability and feasibility are only assessed in the intervention group (as the control group will not experience *i.ARTs*). Scale developers use a moderate effect size (0.3-0.4) to determine sample size. Using the average weighted means and SDs from prior studies [52], we calculated sample size for α=.05, power=0.8 for an independent samples *t* test. Assuming a mean score of 21 (SD 16) in the intervention (*i.ARTs*) group and a mean score of 28 (SD 18) in the control group, the sample size of 90 in each group, for a total of 180, provides 80% power. Our tertiary outcomes are exploratory, but as 35% of US women are not adherent after 6 months, we are powered to detect basic differences between the intervention and control arms.

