### Expected Challenges

As this study is set in real-world clinical settings, we expect challenges to incorporating *i.ARTs* delivery into existing clinical workflows. These include considerations such as available space for participants to complete *i.ARTs*, tech support for the computerized tool and printout, staffing resources, and limited clinician time with each patient to discuss the decision aid results. The study team will work with the clinic staff to determine how to ensure efficient delivery of *i.ARTs* in the clinical setting. Exit interviews will be used to collect data on these challenges to inform further scale-up or dissemination efforts of *i.ARTs* outside of the Miami-based clinic*.*

As LAI ART is being administered in a real-world setting, participating clinicians are subject to existing, and possibly changing, FDA approvals. While phase 3 trials are currently testing LAI ART for nonadherent patients, *the FDA-approved LAI ART formulation is only for virally suppressed patients*. To ensure *i.ARTs* incorporates all relevant drivers of ART use for all women, we aim to include nonadherent women in aim 3, pending FDA approval. If FDA approval only exists for virally suppressed WWH when aim 3 starts, then we will limit the pilot test to that population. Should FDA approval for nonadherent patients begin in the middle of the pilot, we may adjust eligibility criteria to ensure a standard participant population throughout the pilot period. The study team will carefully monitor developments in ART treatment technologies and adapt accordingly. In addition, LAI ART was initially approved as a monthly injection, and the US FDA has approved a bimonthly (ie, every 8 weeks) formulation of LAI ART. This may also affect women’s preferences as the study is rolled out.

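### If entry is limited to virally suppressed women, the planned within-arm change in suppression can essentially only be zero or a fall; attendance has a weaker version of this if the recruitment visit counts at baseline

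*Protocol article*

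**What the plan says.** The Analysis section of the protocol article plans the within-arm comparison twice. It compares decisional conflict, "clinic attendance, viral suppression, and medication refills between and within the 90 women in each arm", using EMR data at 3 and 6 months. It then says that the exploratory tertiary outcomes "viral suppression, clinic attendance, chosen ART modality, and medication refills will compare both between and within" the intervention and control arms. It sets a two-sided 5% level and controls for previous viral load using prebaseline records.

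Two other sections bear on what baseline means for these outcomes.

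- **Suppression.** Expected Challenges notes that at the time of writing "the FDA-approved LAI ART formulation is only for virally suppressed patients", and adds: "If FDA approval only exists for virally suppressed WWH when aim 3 starts, then we will limit the pilot test to that population". The stated aim is still to include nonadherent women if approval allows. The eligibility list in Setting, Participants, Recruitment, and Enrollment has no viral-load criterion. As an outcome, Table 2 gives "Viral suppression, defined as viral load below limit of detection per assay used", and Study Outcomes and Measures uses "viral suppression at the most recent visit in the prior 6 months".
- **Attendance.** Recruitment happens at an attended visit: "A full-time research associate will approach potential participants at their regular clinic visit". Attendance is taken over the previous six months. For oral ART, fewer than two visits in six months counts as a failure (Table 2), and visits fall about every three months (Assessments). The article does not say whether the recruitment visit is counted.

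**The concern.** A before-and-after comparison within one arm is open to regression to the mean when entry depends on the outcome being compared. In an unselected, stable clinic population, women who lose suppression over six months are balanced by women who regain it. If only suppressed women enter, the second group is missing from the sample, so the arm drifts downward even though nothing has changed in the population it came from. Recruiting at a kept appointment can do the same to attendance if that appointment is credited to the baseline window.

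Table 1 describes the EMR data as showing preliminary impact on treatment-related outcomes. A fall in suppression or attendance after i.ARTs could be read as harm. If the recruitment visit were credited to follow-up instead, a gain in attendance could be read as benefit. Either reading could mislead the planning of a later trial. Adjusting for previous viral load does not repair a within-arm change whose starting value was fixed by entry.

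**Working it through.** **Plan's own figures.** The article gives no suppression rate, attendance rate or within-woman correlation, so there is no figure of its own to reproduce on this point. Its only worked power figure is for decisional conflict: 90 per arm, means 21 and 28, SDs 16 and 18. It recomputes to about 78–79% against the stated 80% and does not bear on this point. Everything below is illustration under stated assumptions.

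**1. Suppression, arithmetic of a paired test.** Assume all 90 women in an arm are suppressed at baseline, by the same definition as the endpoint. Every discordant pair is then a loss. With k losses and no gains, the exact two-sided McNemar p is 2 × 0.5^k.

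- k = 5: 2 × 0.5^5 = 0.0625
- k = 6: 2 × 0.5^6 = 0.031, the smallest k below 0.05
- k = 9 (10% of 90): 2 × 0.5^9 = 0.0039

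**2. Suppression with no true change.** Assume population suppression is the same at both times, with a latent normal threshold model and within-woman correlation r. Follow-up suppression among women suppressed at baseline is P(suppressed at both times) / P(suppressed). The chance of a significant decline is P(X ≥ 6), with X binomial on 90 women and the expected fall as its probability.

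| Assumed population suppression | Assumed r | Expected fall, points | Chance of a significant decline in one arm |
|---|---|---|---|
| 65% | 0.5 | 23.6 | over 99% |
| 75% | 0.8 | 10.8 | 93% |
| 85% | 0.8 | 6.9 | 60% |
| 90% | 0.9 | 3.5 | 9% |
| 90% | 0.95 | 2.5 | 2% |

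The direction is the same throughout. The size depends entirely on the assumed inputs.

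**3. Attendance, only if the recruitment visit counts at baseline.** Assume two visits due per six months, each kept with constant probability a, for women on oral ART. At baseline one visit is kept by design, so the chance of fewer than two is 1 − a. At follow-up it is 1 − a².

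- a = 0.85: 1 − 0.85 = 15% at baseline; 1 − 0.7225 = 27.75%, about 28%, at follow-up
- a = 0.70: 1 − 0.70 = 30% at baseline; 1 − 0.49 = 51% at follow-up

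In simulated arms of 90, with visits independent, an exact paired test shows a significant decline in 87%, 78%, 61% and 32% of arms at a = 0.6, 0.7, 0.8 and 0.9. If the recruitment visit is left out, selection on it is roughly symmetric before and after, and the artefact largely goes. A six-month look-back read at month 3 also reaches across baseline, which is a further reason to settle how that visit is counted.

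**4. Between-arm comparison.** With the same follow-up suppression in both arms (80%, 90%, 95%) and 90 per arm, the simulated two-sided type I error of a two-proportion test is 4.9%, 4.9% and 4.3%. Selection at entry creates no false difference between arms.

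**The case against.** The strongest case on the other side has five parts.

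- **No within-arm test is named.** The methods listed compare the two arms or use arm as the main covariate, and the article calls them examples. This stands: the paired test above is an illustration, and descriptive within-arm reporting would fit the present text. But the within-arm comparison itself is stated twice, with a 5% level in the same section and no rule for reading it.
- **The restriction is conditional.** This stands. If nonadherent women enrol, the suppression part falls away. Suppression is also not defined for entry, so baseline may be near 100% rather than exactly 100%. Table 2 further lists an assessment one year before baseline, which entry does not fix.
- **The attendance part needs an unstated counting rule.** This stands. It also uses only the oral-ART definition; women on LAI ART have a different one.
- **The outcomes are exploratory and there is a randomised control arm.** This stands and limits the harm. A fall driven by selection would be expected in both arms.
- **Within-arm change is not purely selection.** Also fair: it would mix selection with any real effect, and the comparison cannot separate them.

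A reader might go further and take the sample-size remark "as 35% of US women are not adherent after 6 months" as the share expected to lose suppression, which would make a spurious decline look almost certain. The article does not support that. The figure concerns adherence, not viral load, and refers to US women generally, not to women enrolled because they are suppressed.

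**Conclusion.** The point holds in conditional form. If entry is limited to suppressed women, as the article says it will be should approval stay as it was at writing, the within-arm comparison of suppression starts at or near its ceiling and can essentially only stay level or fall. This assumes that entry and endpoint use the same or a similar definition of suppression. Under no true change, the expected fall runs from 2.5 to 23.6 points across the assumed inputs, and the chance that one arm would show a significant decline runs from 2% to over 99%. The attendance part is weaker, because it depends on the recruitment visit being counted in the baseline window.

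A reader might infer that the trial's comparison of i.ARTs with standard of care is biased, or that the plan is bound to report deterioration. Neither follows: the randomised contrast is unaffected, and the restriction, the counting rule and the form of any within-arm analysis are all unsettled in the article. With exploratory outcomes, severity is low to moderate.

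**What to change.** In the Analysis section:

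1. State that conclusions about i.ARTs on viral suppression and clinic attendance rest on the randomised between-arm difference at 3 and 6 months.
2. Report within-arm change in these outcomes descriptively only, beside the control arm, with a note that entry fixed or constrained the baseline.
3. Leave the recruitment visit out of both the pre-baseline and the post-baseline attendance counts.

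This is a wording change that needs no new data and no change in sample size. The cost is the loss of any within-arm p-values for these two outcomes.

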#### Study Procedures

##### Randomization

Following informed consent and the baseline assessment (discussed later), we will use a web-based system to randomize women (1:1) to the *i.ARTs* intervention arm (n=90) or to the standard-of-care control arm (n=90). Neither participants nor researchers will be blind to study condition. Women in the control arm will receive standard of care as it exists at the time of LAI ART roll out: providers will offer women information about LAI ART and may strongly suggest which option she should choose. Women who participated in the focus groups will not be eligible for inclusion.

Women in the intervention arm will use *i.ARTs* as part of their regular participant visit. While the complete content of *i.ARTs* will be finalized in phase 2, the web-based *i.ARTs* app will guide WWH through the following activities: (1) provide education on different ART modalities, (2) utilize value clarification methods to guide women in ranking the prominence of relevant barriers and facilitators that may impact adherence to various ART modalities, (3) collect information on participant health history, (4) generate a suggested ART modality based on previous steps, (5) assist WWH in developing questions for their health care providers, and (6) generate an individual profile description as well as individualized suggestions to support adherence based on the modality selected (eg, a woman may be profiled as having transportation challenges; *i.ARTs* would suggest solutions—arranged transportation or transportation vouchers—that the clinic could employ to address these challenges). Participants will take a printout of this profile to their clinic visit with their provider. Intervention arm participants will receive US $15 for *i.ARTs* use.

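### The look at women who do not change regimens selects on a post-randomisation behaviour that the decision aid targets, so a between-arm contrast there can show a small spurious effect in either direction

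*Protocol article*

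**What the plan says.** The Analysis section of Phase 3 sets out the main approach: "The primary analysis will use an intent-to-treat approach". For the tertiary outcomes it states: "Our exploratory tertiary outcomes of viral suppression, clinic attendance, chosen ART modality, and medication refills will compare both between and within" the two arms. The same sentence then adds: "we will also examine these outcomes for women who do not change regimens". Two sentences later it makes regimen choice itself an outcome by arm: "We will also compare how many women in each arm change modalities postbaseline". Between these two statements it plans to control for previous viral load using prebaseline records, and earlier in the section it plans models that control for the Table 2 moderators.

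The Randomization section describes what each arm does to regimen choice. The i.ARTs app will, among other steps, "generate a suggested ART modality based on previous steps". In the control arm, "providers will offer women information about LAI ART and may strongly suggest which option she should choose".

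Expected Challenges notes that "the FDA-approved LAI ART formulation is only for virally suppressed patients" and that, if this is still so when the pilot starts, "then we will limit the pilot test to that population".

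**The concern.** Not changing regimen is known only after randomisation. Both arms act on it, by different routes: a barrier-based suggestion from the tool in one, provider advice in the other. The protocol treats modality change as something that may differ by arm, and then plans an analysis restricted to women without it. Once the subset is formed, randomisation no longer makes the arms comparable within it.

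The tool works by having women rank barriers to adherence. Those barriers plausibly predict later viral suppression, attendance and refills as well. If i.ARTs moves a different kind of woman to injectable treatment than usual care does, the women who remain differ in prognosis between arms even if the tool changes nobody's suppression.

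Because the subset keeps the randomised arm labels, its result could be taken for the effect of i.ARTs on women who stay on their regimen, when it may partly show who left. This also separates it from the planned analysis by treatment actually taken, which plainly regroups the women. One of the listed outcomes, chosen modality, cannot vary through switching among women selected for not switching.

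**Working it through.** **Plan's own figure.** There is none for this analysis. The only stated power is 80% for decisional conflict with 90 per arm. It is not in dispute: SD = √((16² + 18²)/2) = 17.03, standardised difference 7/17.03 = 0.411, and the normal approximation gives 78.7%. It has no bearing on the non-changer subset.

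**Inputs.** From the documents: 90 women per arm, and suppressed-only enrolment if the approval is unchanged. Everything else is assumed, because the documents give no switching rates and no suppression rates by type of woman:
- two equal groups of women, with 6-month suppression of 95% (good prognosis) and 75% (poor prognosis);
- no effect of arm on any woman's suppression;
- 10% switching in both groups of the control arm, and in one group of the i.ARTs arm;
- 40% or 60% switching in the other group of the i.ARTs arm.

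**Formula.** With group share w, switching rate s and suppression p, suppression among non-changers in an arm is Σ w(1 − s)p / Σ w(1 − s).

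**All randomised women.** 0.5 × 0.95 + 0.5 × 0.75 = 85.0% in both arms, whatever the switching pattern. The difference is 0.

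**Control non-changers.** (0.45 × 0.95 + 0.45 × 0.75)/0.90 = 85.0%, with 81 women expected.

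**i.ARTs non-changers.**

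| Who switches more under i.ARTs | Calculation | Suppressed | Difference from control | Two-sided rejection (nominal 5%) |
|---|---|---|---|---|
| Good prognosis, 40% | (0.30 × 0.95 + 0.45 × 0.75)/0.75 | 83.0% | −2.0 points | 6.4% |
| Poor prognosis, 40% | (0.45 × 0.95 + 0.30 × 0.75)/0.75 | 87.0% | +2.0 points | 6.3% |
| Good prognosis, 60% | (0.20 × 0.95 + 0.45 × 0.75)/0.65 | 81.2% | −3.8 points | 9.6% |
| Poor prognosis, 60% | (0.45 × 0.95 + 0.20 × 0.75)/0.65 | 88.8% | +3.8 points | 9.5% |

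Rejection is for an unadjusted pooled z test at the expected numbers of non-changers.

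**Switching unrelated to prognosis.** With 40% switching in both groups under i.ARTs: (0.30 × 0.95 + 0.30 × 0.75)/0.60 = 85.0%. The bias is zero, although far more women switch than in control.

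**Equal switching, different women.** Let 20% switch in each arm: 30% good and 10% poor in control, the reverse under i.ARTs. Control is (0.35 × 0.95 + 0.45 × 0.75)/0.80 = 83.75%; i.ARTs is (0.45 × 0.95 + 0.35 × 0.75)/0.80 = 86.25%. The difference is +2.5 points, so equal counts of switchers do not make the subset safe.

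**A version in terms of barriers.** Assume 40% of suppressed women have pill barriers, with 6-month suppression of 80% with barriers and 97% without. Assume injectable uptake of 60% and 10% respectively under i.ARTs, and 20% in both groups in control. Non-changers are (0.16 × 0.80 + 0.54 × 0.97)/0.70 = 93.1% under i.ARTs and (0.32 × 0.80 + 0.48 × 0.97)/0.80 = 90.2% in control, a spurious +2.9 points. With about 63 and 72 women the standard error is about 4.7 points, and rejection is about 9%.

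**The case against.** **The text does not state a between-arm test.** The verb in the clause is open, and a within-arm description of non-changers would satisfy it. This stands as a caution. A reader might infer that a between-arm test in this subset is fixed; the documents do not go that far. The clause does continue a sentence about comparing between and within arms, so the between-arm reading is the natural one and nothing in the text excludes it.

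**A much larger bias is tempting to infer, and the documents do not support it.** Suppose 80% of women are suppressed at entry, only they may move to injectable treatment, and 40% (i.ARTs) against 15% (control) of them do. Non-changers are then 0.48/0.68 = 70.6% against 0.68/0.88 = 77.3% suppressed, 6.7 points apart. Varying such assumptions gives 2.7 to 11.7 points. This needs unsuppressed women in the trial while injectable treatment is closed to them, a combination that Expected Challenges largely rules out by limiting the pilot to suppressed women in that event. The eligibility list has no suppression criterion, and Table 2 counts injectable adoption among suppressed women, so some mixing is conceivable. Even then, the example holds each woman's status fixed, so the planned control for previous viral load would remove the difference if it captures baseline status. That range should not be used.

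**Adjustment is planned.** Several Table 2 moderators, such as housing, distance from clinic, substance use and self-efficacy, are barriers of the relevant kind, and controlling for them would reduce the bias. This is partly right. It removes only what is measured and modelled well, and if all women are suppressed at entry, control for previous viral load removes little.

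**The stakes are low.** These are exploratory tertiary outcomes in a pilot whose primary outcomes are feasibility, acceptability and usability. This stands and sets the severity. Against it, the Power Analysis section also claims power for basic between-arm differences on these outcomes, which invites an inferential reading.

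**Caveats may sit in a fuller document.** They may, and their absence here is no fault. The point concerns the analysis that the article does state.

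**Conclusion.** The point holds in a limited form. Read as a between-arm comparison, the non-changer analysis conditions on a behaviour that i.ARTs is designed to alter, and it cannot be interpreted as an effect of the tool on women who stay on their regimen. In a suppressed-only population the unadjusted spurious difference is about 2 to 4 points, in a direction that cannot be known in advance. The size rests wholly on assumed switching and suppression rates. It requires that switching depends on prognosis and does so differently in the two arms; without that it is zero. Measured-covariate adjustment would shrink it by an unknown amount. The comparison of all randomised women is unaffected. Severity is modest: worth correcting before the trial starts, but no threat to its main conclusions.

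**What to change.** Reword the one clause in the Analysis section:
- Base every between-arm statement on viral suppression, attendance and refills on all randomised women, or on subgroups defined from baseline data alone (for example, women on oral ART at baseline), analysed as randomised.
- Report women who do not change regimens only descriptively within each arm, labelled as a non-randomised subset, with their baseline characteristics shown.

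No new data are needed. The cost is that there is no between-arm test among non-changers.
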